#### Analysis

Various comparative analyzes will be performed using data obtained from both groups and excluded from follow-up.

### Procedure

#### Stage 1

In the first stage, understandability, usability and adequacy of CDSMS software will be tested. 5 physicians will test CDSMS on at least 16 diabetes patients. The system will be revised according to the comments received on the Web Site Usability Test [38] and feedback form.

#### Stage 2

At this stage, a randomized controlled trial will be performed. Firstly, the physicians who manage the treatment of the patients will register online through the web based portal for free. The researchers will train these physicians about the use of portal.

Patients who are referred to select family medicine centers for any reason will receive diabetes screening using CDSMS. The patients who were previously diagnosed as diabetics will be recruited for trial by the physicians. The recruited patients will register to the CDSMS via mobile phone or web page with the accounts provided by their physicians, free of charge.

The proposed clinical decision support system is a recommended tool for primary care physicians to make clinical decisions on screening, diagnosis, treatment and monitoring of DM patients. Physicians input the data of patients having FPG, HbA1c or PPG test results in last six months. CDSS will make a statement on diagnosis of patient and/or stage. The system will also suggest a treatment plan for the patient. The physician will evaluate the system’s recommendations and decide on a treatment for the patient and input his/her treatment decision. CDSS will suggest a monitoring plan to the physician. The physician will evaluate the proposals and input the monitoring plan that he/she has decided for the patient into the system. The follow-up visits will happen with the physician. There are two options for carrying out the monitoring process:

The first is installing the developed mobile application. Patients will install the application on their mobile phone and complete the online registration process. They will be trained about how to access and use the program and how to input their data into the daily program on the application. They will be given a brochure which briefly explains the program. Then, usual patient examination process will be completed. Patients will input their measurement data (e.g. FPG, diet, exercise, weight) regularly or these data will be transferred automatically from sensors to the system via communication technologies such as Bluetooth, Wi-Fi etc. (Figure 2). Through mobile application, patients can receive individualized therapy as well as alerts and notifications such as the amount and frequency of use of medicines on their monitoring process.

**Fig. 2 Fig2:**
[figure not shown]
Tele-monitoring system

The second is using a transfer device developed for this study. The transfer device will be developed for especially elderly patients who are not able to use smart phones. It is specialized for data collection and transferring. This device will read data automatically from sensors which have communication ability (e.g. Bluetooth) or measured values will be entered manually via large buttons for the ease of use for the elderly.

These options will allow patient data to be transferred to the system periodically from either a mobile application or a transfer device. Regularly collected data will be used for physician’s evaluation. Notifications will be sent via web and mobile application to the physician and/or patient when deviations from the normal state occur. Notification messages will be in the form of reminders, including reminders to take medication, follow the diet, and complete exercise. It will also notify the patient when blood sugar is high, and will notify both the patient and the physician if the patient is experiencing a risky situation such as hyperglycemia or hypoglycemia. The CDSMS will generate the notifications according to the patient’s input, processing the algorithms defined in the system according to the evidence based guidelines. In accordance with the patient data in the system, notices and short reports will be created for physician and patient in certain periods of time.

For patient security, personal information will be kept encrypted. In addition, technologies such as https, VPN will be used during the secure access to the system. Access rights to the system will be determined by user role definitions.

When testing CDSMS, the system will make a suggestion to the physician. The physician will make his/her own decision on the patient considering the system’s suggestion and his/her clinical experience. Both the suggestion of CDSMS and physician’s own decision will be saved in system and compared later. Physicians will take suggestion of CDSMS but implement their own decision for each case. The application is designed in this specific way in order to avoid any harm on patients.

No side effects are expected depending on the intervention. However, the intervention is discontinued due to hospitalization in cases of diabetes or other illnesses. In addition, the intervention is ended due to participant request or death.

There is no plan for terminating the trial. Because there is no specific risk or harm expected from the intervention. If a disease other than diabetes occurs during the trial, the routine health care necessary for the treatment of the disease is applied.

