### Measures

Primary outcomes of RCT include HbA1c, Fasting Blood Glucose and Postprandial Blood Glucose levels. Secondary outcomes include body mass index, diabetes-related emotional burden and interpersonal distress sub-scales, self-efficacy for diabetes self-care, blood glucose monitoring, physical activity, nutrition, medication-taking, diabetes self-care: blood glucose self-monitoring, medication-taking, smoking and alcohol using and physical activity, depression, anxiety, stress levels. Clinical and laboratory outcomes will be face-to-face assessed, others will be online self-assessed. The effectiveness of the system will be evaluated by using primary and secondary outcomes.

Table 2 lists all the outcomes and measures used in this study. Fasting blood glucose, HbA1c and other tests according to patient history and physical examination will be determined and implemented for each patient taken into intervention and control groups. Body mass index of patients will be calculated. On baseline all scales will be implemented online such as Diabetes Distress Scale [40], Diabetes Self-Efficacy Scale [41], Diabetes Self-Care Activities Survey [42], Morisky Medication Adherence Scale [43], The Patient Assessment of Chronic Illness Care-Patient Form [44, 45]. Monthly average of FPG and PPG values of patients regularly taken from the tele-monitoring system will be evaluated. Glycosylated hemoglobin (HbA1c) test will be done quarterly.

**Table 2 Tab2:** Measures

Measurement area	Outcomes assessed	Measure/s
Demographics	Age, gender, nationality, country of birth, relationship status, employment status, health insurance	Short answer and multiple choice items
Laboratory	Glycosylated hemoglobin A1c (HbA1c) level Fasting And Postprandial Blood Glucose	Venous blood sample
Clinical	Height, Weight, Diabetes Symptoms, Risk Factors	Patient history and physical examination
Emotional/ Psychological	Depression, anxiety, stress levels Diabetes-related emotional burden and interpersonal distress sub-scales Self-efficacy for diabetes self-care: blood glucose monitoring, physical activity, nutrition, medication-taking	Diabetes Distress Scale [40] Diabetes Self-Efficacy Scale [41]
Behavioral	Physical activity Diabetes self-care – blood glucose self-monitoring, medication-taking, smoking and alcohol using and physical activity	Diabetes Self-Care Activities Survey [42] Morisky Medication Adherence Scale [43]

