## Discussion

This study describes the first comprehensive clinical decision support system intended for diabetes screening, diagnosis, treatment and monitoring in Turkey. Moreover, this clinical decision support and monitoring system using evidence-based guidelines will pave the path for other medical specialties providing health services to diabetes patients. In addition, remote monitoring of patient data and alert mechanisms are also implemented in this study. Patient adherence to treatment in medication and lifestyle changes will be provided.

Using CDSMS based on current diabetes guidelines and telemonitoring systems will provide patients a means to receive effective treatment and regular monitoring. This will reduce possible complications, hospitalization, morbidity, and mortality caused by diabetes while also reducing the cost of treatment.

Electronically monitoring period screenings will provide early diagnosis and protection from potential diseases. This will enable patients to live longer and healthier lives, reduce treatment costs, and prevent the labor loss.

In CDSMS, patients actively participate in their treatment by regularly inputting measurement values and receiving motivational and reminder messages. Constant communication will increase the patient’s self-efficacy, thereby reducing emotional stress and increasing the patient quality of life.

Information technologies are integrated to patient care and monitoring in primary health care services with the proposed CDSMS based on predictive modeling. This new comprehensive and integrated approach will contribute to rapidly evolving e-health technology in the world using national information and technology savings. In addition, patient data will be collected when using rule based CDSMS. As a future study, an intelligent clinical decision support system will be developed using machine learning and artificial intelligence technologies on collected data.

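### The plan expects no harm from a system that advises on diabetes treatment, and its outcome list would give no between-arm information on hypoglycaemia or hospital admission

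*Protocol article*

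**What the plan says.** All references are to the protocol article.

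- **Expectation of harm (Procedure, Stage 2).** "No side effects are expected depending on the intervention", and then: "There is no plan for terminating the trial. Because there is no specific risk or harm expected from the intervention". The absence of expected harm is the stated reason for a design decision.
- **What the system does (Procedure, Stage 2).** For the physician: "The system will also suggest a treatment plan for the patient". On the patient's side: "patients can receive individualized therapy as well as alerts and notifications such as the amount and frequency of use of medicines on their monitoring process". The system also "will notify both the patient and the physician if the patient is experiencing a risky situation such as hyperglycemia or hypoglycemia".
- **Safeguard (Procedure, Stage 2).** The system only advises. The physician decides each case, and the article says the design was chosen to avoid harming patients.
- **Hospital admission.** It appears in the Procedure as a reason for stopping: "the intervention is discontinued due to hospitalization in cases of diabetes or other illnesses". It appears again in the Discussion as an expected benefit.
- **Outcomes (Measures, Tables 2 and 3).** The primary outcomes are HbA1c, fasting glucose and postprandial glucose. Effectiveness is judged on the primary and secondary outcomes, and Table 2 is said to contain every outcome and measure used. On home readings: "Monthly average of FPG and PPG values of patients regularly taken from the tele-monitoring system will be evaluated".
- **Control arm (Allocation; Measures).** Seven physicians treat controls without the system, and care continues as before.

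**The concern.** Each primary outcome improves when glucose falls. If the system leads physicians or patients to intensify treatment, average glucose and HbA1c may fall while some patients have more low episodes. A fair reading of the result then needs a count of those episodes in both arms.

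The plan as written provides none. Its expectation of no harm sits beside a function that treats hypoglycaemia as dangerous enough to alert two people. Of the two dangerous states it names, high glucose shows in the outcomes and low glucose does not. Any hypoglycaemia counts that emerged from the alert log would come from one arm only. At stake is whether a positive HbA1c result can be presented together with any comparative statement about harm.

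**Working it through.** **1. Search of the outcome list.** Table 2 covers demographics, HbA1c and glucose from venous blood, height, weight, diabetes symptoms, risk factors, psychological and behavioural scales, satisfaction with therapy, and program usability. It has 0 items for hypoglycaemia, 0 for hospital admission and 0 for adverse events. The diabetes-symptoms entry does not fill the gap: the text on Stage 2 participants defines these as symptoms of diabetes such as polyuria, polydipsia and fatigue, not as hypoglycaemic episodes. The content of Table 3 is not visible, but the text describes it as a summary of when the measures and scales are taken.

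**2. Effect of averaging (illustrative readings).** Thirty fasting readings in a month, 28 at 130 mg/dl and 2 at 50 mg/dl:

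(28 × 130 + 2 × 50) / 30 = 3740 / 30 = 124.7 mg/dl.

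A patient steady at 130 has a mean of 130. The patient with two low readings looks better by 5.3 mg/dl.

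**3. Arm sizes.** The plan gives no safety figure to reproduce, but its arm sizes are the inputs below, so I checked them. Inputs: 25% controlled in the control arm, odds ratio 2 (hence 40%), 80% power, 5% significance (taken as two-sided), ratio 1:3. The pooled proportion is (0.40 + 3 × 0.25)/4 = 0.2875. With the Kelsey formula:

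n = (1.960 + 0.842)² × 0.2875 × 0.7125 × (4/3) / 0.15² = 95.28 intervention, and 3 × 95.28 = 285.83 control.

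Multiplying by 1.15 gives 109.6 and 328.7, so 110 + 329 = 439, as stated.

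**4. What a two-arm count could show.** The document gives no event rates. Assume, for illustration only, that 10% of intervention and 5% of control patients report any hypoglycaemia over 6 months.

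- All randomised: SE = √(0.10 × 0.90/110 + 0.05 × 0.95/329) = 0.0310; 1.96 × SE = 6.1 points.
- After loss, dividing by 1.15 as the stated total implies (96 and 286): SE = 0.0332; ±6.5 points.
- After loss of 15% of those randomised (93 and 280): SE = 0.0337; ±6.6 points.

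Power to detect a doubled risk at 110 against 329, by assumed control rate:

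| Control rate | Power |
|---|---|
| 1% | 17% |
| 2% | 25% |
| 5% | 47% |
| 10% | 75% |

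With no events among 110 intervention patients, the one-sided 95% upper bound is 1 − 0.05^(1/110) = 2.7%.

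None of these figures allows for clustering by physician. With three physicians in one arm and seven in the other, the true intervals are probably wider.

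**The case against.** The strongest reply is that the two statements are about different things. The article says no harm is expected from the intervention, whereas the alert concerns a state the patient may be in because of the disease, which the system exists to detect. Physician discretion is a real safeguard. That much stands: the article never calls hypoglycaemia a risk of the system, and a reader should not infer that it does, or that the system is unsafe. But discretion limits harm without measuring it, and the trial is run because the system is expected to influence decisions.

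A second reply is that an article condenses a fuller protocol, which may describe adverse-event recording. This too stands in part: one cannot conclude that no adverse event will be recorded anywhere. But the article presents Table 2 as the full list of outcomes and gives the no-harm premise as its reason for having no termination plan. Those are statements, not omissions through brevity.

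Three further readings are tempting and are not supported.

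- The hospitalisation rule might look one-sided. It stops the intervention, so it cannot have a counterpart among controls.
- The Discussion says of the system: "This will reduce possible complications, hospitalization, morbidity, and mortality caused by diabetes while also reducing the cost of treatment". That is a hope about long-term benefit and not a planned inference, so the trial is not at fault for leaving it untested.
- Averaging need not mean that individual low readings are lost. They reach the physician through alerts. The point is only that the summary to be evaluated does not show them.

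Finally, the trial is too small to establish safety. This is true, and it is a reason to estimate with intervals rather than to collect nothing.

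**Conclusion.** The point holds. The expectation of no harm does not fit with the treatment advice, medicine messages and hypoglycaemia alerts described in the same section, and the outcome list contains nothing that would test it. If the plan is followed as written, a lower HbA1c could be reported with no between-arm information on hypoglycaemia or admissions.

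The size of any harm is unknown, because the document gives no rates. Under the assumed 10% and 5%, the trial would estimate a 5-point difference to within about ±6 points, or about ±6.5 after loss, before clustering. That is useful for description but not for showing safety.

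The conclusion rests on two readings. One is that Table 2 is complete, as the article says. The other is that control patients have no tele-monitoring or alerts, as Allocation and Measures indicate. It also takes advice on diabetes treatment to include glucose-lowering treatment, which is an inference from the text.

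**What to change.** 1. Reconcile the no-harm statements in the Procedure with the treatment suggestions, medicine messages and hypoglycaemia alerts described there, including the use of that premise as the reason for having no termination plan.
2. Add two descriptive safety outcomes to Tables 2 and 3: (a) patient-reported hypoglycaemia, with episodes needing another person's help identified separately; (b) hospital admission or emergency visit, with cause.
3. Ask both with the same fixed questions in both arms at baseline and month 6, and at the quarterly HbA1c test where both arms attend.
4. Report them by arm as randomised, with confidence intervals, beside the HbA1c result. Include patients whose intervention stopped, in line with the intention-to-treat analysis already planned.
5. Do not use app alerts for the between-arm comparison. Report the count of low readings in the intervention arm separately, alongside the monthly averages.

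**Cost.** Two short sets of questions, one results table and a wording change, with a little more data entry. Quarterly attendance by controls is not established in the article, so only baseline and month 6 can be relied on.

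**Limits to state in the report.** Alerts and prompted monitoring may lead intervention patients to recognise and report more episodes, so identical questions will not give identical ascertainment. Episodes needing help, and admissions, are the less biased comparison. Precision is low, and a non-significant difference must not be read as evidence of safety.

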### Measures

Primary outcomes of RCT include HbA1c, Fasting Blood Glucose and Postprandial Blood Glucose levels. Secondary outcomes include body mass index, diabetes-related emotional burden and interpersonal distress sub-scales, self-efficacy for diabetes self-care, blood glucose monitoring, physical activity, nutrition, medication-taking, diabetes self-care: blood glucose self-monitoring, medication-taking, smoking and alcohol using and physical activity, depression, anxiety, stress levels. Clinical and laboratory outcomes will be face-to-face assessed, others will be online self-assessed. The effectiveness of the system will be evaluated by using primary and secondary outcomes.

Table 2 lists all the outcomes and measures used in this study. Fasting blood glucose, HbA1c and other tests according to patient history and physical examination will be determined and implemented for each patient taken into intervention and control groups. Body mass index of patients will be calculated. On baseline all scales will be implemented online such as Diabetes Distress Scale [40], Diabetes Self-Efficacy Scale [41], Diabetes Self-Care Activities Survey [42], Morisky Medication Adherence Scale [43], The Patient Assessment of Chronic Illness Care-Patient Form [44, 45]. Monthly average of FPG and PPG values of patients regularly taken from the tele-monitoring system will be evaluated. Glycosylated hemoglobin (HbA1c) test will be done quarterly.

**Table 2 Tab2:** Measures

Measurement area	Outcomes assessed	Measure/s
Demographics	Age, gender, nationality, country of birth, relationship status, employment status, health insurance	Short answer and multiple choice items
Laboratory	Glycosylated hemoglobin A1c (HbA1c) level Fasting And Postprandial Blood Glucose	Venous blood sample
Clinical	Height, Weight, Diabetes Symptoms, Risk Factors	Patient history and physical examination
Emotional/ Psychological	Depression, anxiety, stress levels Diabetes-related emotional burden and interpersonal distress sub-scales Self-efficacy for diabetes self-care: blood glucose monitoring, physical activity, nutrition, medication-taking	Diabetes Distress Scale [40] Diabetes Self-Efficacy Scale [41]
Behavioral	Physical activity Diabetes self-care – blood glucose self-monitoring, medication-taking, smoking and alcohol using and physical activity	Diabetes Self-Care Activities Survey [42] Morisky Medication Adherence Scale [43]
Patient therapy evaluations	Patients’ satisfaction with therapy	The Patient Assessment of Chronic Illness Care-Patient Form [44, 45]
User program evaluations	Users’ program usage, perceived utility and acceptability, ease of use, user interface, and satisfaction with program	Web Site Usability Scale [38] Feedback form

Participants in the intervention group will be given screening, diagnosis, treatment and monitoring services by the physicians using CDSMS for six months. These patients will be monitored in the framework of the protocols. The control group patients will receive services from physicians as they have done before without further intervention. All tests and scales implemented on screening and baseline will be repeated at the end of six months. By comparing the two groups, the effectiveness of the study will be measured. The measures and scales used at screening (enrollment), baseline, monthly, quarterly and at the end of intervention are summarized in Table 3.

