• Over age 40 • Volunteer • Computer and Internet literacy • DM diagnosed or having at least one of diagnostic criteria. These criteria; • HbA1c ≥ 6.5 • FPG ≥ 126 mg / dl • 2-h postprandial glucose ≥200 mg / dl • Any time postprandial glucose ≥200 mg / dl • Diabetes symptoms	• Having communication problems • Type 1 diabetes • MODY type DM • Psychotic disorders • Dementia

### Stage 2

In the second stage, the health data of 3000 participants will be evaluated to determine the effectiveness of CDSMS in screening. Participants who use medicine for DM treatment will be excluded from data analysis when measuring the effectiveness of the system in screening.

Patients who applied to primary health care services for any reason and screened within the scope of periodic health care for diabetes, having at least one measurement of FPG (Fasting Plasma Glucose), HbA1C or PPG (Postprandial Plasma Glucose) in last six months will be participants of stage 2. Participants determined in second phase will be evaluated in terms of inclusion and exclusion criteria. Eligible and volunteer participants will take part in the trial. Inclusion and exclusion criteria for randomized controlled trial are listed below in Table 1.

Patients who were diagnosed with DM among 3000 participants (new diagnosis, former diagnosis, medicine users, non-medicine users) will form the population of the randomized controlled trial. The sample size evaluated by significance level *p* = 0.05, 80% power, 25% prevalence (controlled diabetes) and odds ratio 2 will be included to experimental study. Because in RCT studies lost to follow up is approximately 15.0%, this amount is taken into account for determining the sample size. The sample contains 439 patients with 110 interventions and 329 control groups. The ratio of intervention to non-intervention (controls) is 1:3. About 3000 people over age 40 apply to the 10 primary health care units (In the city of Izmir in Turkey) in a month. For reaching expected number of samples, at least %14 of patients are thought to be eligible for inclusion criteria. (assuming DM prevalence approximately 14%).

Diabetes symptoms aforementioned in Table 1 are classical symptoms of polyuria, polydipsia, polyphagia or loss of appetite, weakness, fatigue, dry mouth, nocturia. Less common symptoms are blurred vision, unexplained weight loss, persistent infections, recurrent yeast infections and itching [10].

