### Statistical analysis

Statistical analysis will be performed using SPSS software. As stated in the method section, the system will be tested in two stages.

### Stage 1

For the first stage, the comments in the feedback forms will be used for revisions of program. Descriptive analyzes will be done for web site usability test results.

### Stage 2

At the end of the intervention, independent samples t-tests will be performed to measure the difference between the intervention and control groups. On both groups, one-sample t-test will be performed to measure the difference between baseline and post intervention in the same group.

Each of the dependent measures of primary outcomes will be analyzed using a generalized linear mixed model involving a single between Group factor (Treatment vs. Control), a single within Period factor (enrollment vs. end of 6 months), and interaction between Group and Period factor. Categorical data of both control and intervention groups will be analyzed together using logistic regression. The rates of controlled and uncontrolled diabetes patients will be determined.

An intention-to-treat analysis will be performed. The analysis will include all individuals’ data. In the analysis, patients will be compared regardless of patient compliance, crossover to other treatments, or withdrawal from the study.

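### The sample size and its 80% power are for a binary controlled-diabetes endpoint that is not a declared outcome; power for the three declared continuous primaries is undocumented, and no rule says which of them decides success

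*Protocol article*

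**What the plan says.** **Sizing endpoint** (Participants and sample size, Stage 2): "The sample size evaluated by significance level *p* = 0.05, 80% power, 25% prevalence (controlled diabetes) and odds ratio 2". A 15% loss to follow-up is then allowed for, and the result is given as: "The sample contains 439 patients with 110 interventions and 329 control groups".

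**Declared outcomes** (Measures): "Primary outcomes of RCT include HbA1c, Fasting Blood Glucose and Postprandial Blood Glucose levels". The secondary list covers body mass index, distress, self-efficacy, self-care behaviour and mood. Controlled diabetes is in neither list and not in Table 2. The same section adds: "The effectiveness of the system will be evaluated by using primary and secondary outcomes".

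**Analysis** (Statistical analysis, Stage 2): "Each of the dependent measures of primary outcomes will be analyzed using a generalized linear mixed model", with group, period and their interaction as terms. Independent-samples t-tests between the groups are planned as well. Categorical data go to logistic regression, and of the sizing endpoint the section says only: "The rates of controlled and uncontrolled diabetes patients will be determined".

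**Significance level**: the Abstract sets p < 0.05. No other level, testing order or success rule appears.

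**Definition of controlled**: an HbA1c value below 7% is mentioned only in the Background, where the share of diabetic patients who reach it is given as 30.1%. The Methods state no cut-off.

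**The concern.** A power statement is useful only for the outcome on which the trial will be judged. Here the outcome that fixed the sample size and the outcomes called primary are different quantities: one proportion against three means. No mean difference and no SD is given for HbA1c, fasting glucose or postprandial glucose, so a null result on any of them could not be read against a stated target.

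The second issue follows from having three primaries without a decision rule. A difference on one glucose measure alone could later be presented as showing that the system works, and the general sentence on judging effectiveness does not close that route. How often this would happen by chance depends on the rule, and the article does not state one.

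**Working it through.** **1. Reproduce the plan's figure.** Inputs from Participants and sample size: 25% controlled, odds ratio 2, alpha 0.05 (taken as two-sided; the article does not say), 80% power, allocation 1:3, 15% loss.

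- Intervention proportion: odds = 2 × 0.25/0.75 = 0.667, so p₁ = 0.667/1.667 = 0.40.
- Pooled proportion: (0.40 + 3 × 0.25)/4 = 0.2875.
- Kelsey formula: n₁ = (1.960 + 0.842)² × 0.2875 × 0.7125 × (4/3) / 0.15² = 95.3 intervention. Controls: 3 × 95.3 = 285.8.
- Multiply by 1.15: 109.6 and 328.7, rounded up to 110 + 329 = **439**.

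The figure reproduces exactly, so the calculation is clearly for a difference in proportions. (The alternative reading, 25% in the intervention arm and 14.3% in control, needs 548 by the Fleiss formula before any loss and does not lead to 439.)

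**2. Compare endpoint with outcomes.**

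| | Sample size section | Measures section |
|---|---|---|
| Quantity | Proportion controlled | Levels of HbA1c, fasting and postprandial glucose |
| Number | One | Three |
| Effect assumed | 25% vs 40% | None stated |
| Status | Not listed as an outcome | Primary |

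**3. What 439 patients can detect on a continuous primary.** With 15% lost, 110 × 0.85 ≈ 93 and 329 × 0.85 ≈ 280. For a simple comparison of final means:

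detectable difference = 2.80 × √(1/93 + 1/280) = 2.80 × 0.1197 = **0.34 SD**.

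Power at 0.05 for true differences of 0.2, 0.3 and 0.4 SD is 39%, 71% and 92%. Physician clustering is ignored.

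The planned group-by-period interaction compares changes from baseline. With equal variances, the 0.335 is then multiplied by √(2(1 − r)), where r is the correlation between baseline and month 6: 0.40 SD at r = 0.3, 0.34 at r = 0.5, 0.26 at r = 0.7. The article gives no r; these values are assumptions.

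**4. The plan's own effect put on a continuous scale (illustration).** Suppose 25% versus 40% controlled came from a shift in a normal HbA1c distribution with equal SDs. The shift is z(0.40) − z(0.25) = −0.253 + 0.674 = 0.42 SD. Power for the final means is Φ(0.421/0.1197 − 1.960) = Φ(1.56) ≈ 94%.

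**5. False-positive chance for at least one of three tests at 0.05.** If independent: 1 − 0.95³ = 14.3%. For three equally correlated normal test statistics (the correlations are assumed; none is in the article):

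| Correlation | 0 | 0.3 | 0.5 | 0.7 | 0.9 |
|---|---|---|---|---|---|
| At least one of three | 14.3% | 13.6% | 12.5% | 10.9% | 8.4% |

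If all three must be significant, the chance is at most 5%. If they are tested in a fixed order, stopping at the first failure, it is also at most 5%.

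**The case against.** Two stronger readings are tempting, and the article supports neither.

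*That the trial is underpowered.* The stated 80% reproduces for its own endpoint. For the primaries, nothing shows that power is low. Under the shift assumption in step 4, mean HbA1c would have about 94% power, because a continuous measure uses more of the information than its dichotomy. This objection stands: what can be said is that power is unstated.

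*That the false-positive rate exceeds 5%.* This holds only if one significant primary is enough, and no sentence says so. The sentence on judging effectiveness by primary and secondary outcomes is general and does not say that a single result can carry the claim. A testing order or adjustment may also stand in an analysis plan that is not shown. This stands too, so the error rate can be given only conditionally. Independence is moreover an extreme case for three measures of glycaemia.

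It can also be argued that controlled diabetes is simply HbA1c dichotomised: the Background calls HbA1c a marker of glycaemic control, and the article does plan logistic regression for categorical data. That is a plausible reading, but it does not remove the mismatch. The Methods neither state the cut-off nor list the dichotomy as an outcome, and the primaries are named as levels. An analysis plan could add a multiplicity rule. It could not make the sample size calculation apply to the declared primaries without changing one of the two sections.

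**Conclusion.** The point holds as a mismatch between two statements that the article itself makes. The 80% power applies to 25% versus 40% controlled diabetes, which is not a declared outcome and has no cut-off in the Methods. For the three declared primaries power is undocumented, not shown to be inadequate. A reference value is 0.34 SD with 93 versus 280 evaluable patients, which rests on two-sided 0.05, 15% loss, a comparison of final means and no physician clustering.

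The multiplicity part is conditional: about 8% to 14% for at least one false positive if any one primary suffices (correlations from 0.9 down to 0), and at most 5% if all three are required. The article leaves open which of these applies.

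**What to change.** Make the primary outcome and the sizing endpoint the same before analysis. Either route works:

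1. Declare controlled diabetes at month 6, with its HbA1c cut-off written into the Methods, as the single primary outcome. The existing calculation then applies.
2. Name HbA1c at month 6 as the single primary, or fix the testing order HbA1c, fasting glucose, postprandial glucose. Restate the power or detectable difference for 439 patients on that outcome and for the model that will be used.

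Treat the remaining outcomes as secondary, and tie the claim of effectiveness to the primary. An alpha split or an all-three rule would also settle the error rate, but a split has a price: at 0.05/3 = 0.0167 the detectable difference rises from 0.34 to 0.39 SD.

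The change is one of wording in the protocol and analysis plan and needs no new data. The cost is a narrower claim: a result on a single glucose measure or questionnaire could no longer stand for the effectiveness of the system.
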